#### Secondary outcome measures

Self-reported levels of suicidality, depression, anxiety, stress, resilience, problem-solving skills, and self- and therapist-reported level of therapeutic engagement are measured. Scores will be compared for each group at each follow-up time point. A cost comparison will also be done for both interventions (compared to TAU), and estimates will be based on service information regularly collated by GCMHSS and ED (e.g. contact hours, bed stays, ED visits). We expect a low completion rate (see the “Sample size” section). Study completion will be analysed post hoc, as a secondary outcome.

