### Sample size {14}

The sample size was calculated on the basis of a time to event analysis of the time to representation for suicidality. From previous studies using CBT as an additional treatment component following attempted suicide [24, 39], we anticipated that the proportion of patients re-presenting for attempted suicide over a 2-year follow-up period will be approximately half that of the TAU group. From recent data from our health service, this represents a decrease from 48 to 24%. To detect this difference (equivalent to a hazard ratio of 0.42) by the log rank test in a proportional hazards time-to-event analysis with 80% power at a two-sided significance level of 5%, we require 132 participants in two groups of 66 each. However, we anticipated a dropout rate of approximately 4.5% per month which would result in 35% of participants completing the full 24-month follow-up (65% total dropout). The effective dropout rate is thus 41%, as those dropping out later contribute proportionately more. When accounting for this dropout rate, to maintain the same power, a total of 137 participants in each of the three cohorts are required for a total of 411 in total.

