### Data collection and management

#### Plans for assessment and collection of outcomes {18a}

Each person who presents to Gold Coast Health is assigned a unique identifying, or UR, number. The Emergency Information System at Gold Coast Health (viz., FirstNet database) records all ED presentations. The ED presentations will be interrogated for the UR number of all study participants, and any presentation within 24 months of an initial presentation will be reviewed for evidence of suicidality. Multivariate Cox proportional hazard regression models will be used to analyse time to re-presentation for a suicide attempt. Time to suicide attempt is measured by calculating the total number of days from the initial presentation (not including days of admission for some consumers with medical and/or psychiatric admission) to the re-presenting date for a subsequent suicide attempt.

For secondary outcomes, data are collected by the RA at five time points: (1) baseline, (2) end of CBT or ASSIP interventions, (3) 6 months, (4) 12 months, and (5) 24 months from baseline. At baseline, demographic data and psychometric data are collected in person or via the telephone with the RA, as outlined below. At end of treatment and 6, 12, and 24 months, psychometric data are collected. Therapeutic alliance is assessed at the completion of the interventions. Cost comparisons will be based on service information regularly collated by GCMHSS and ED (e.g. contact hours, bed stays, ED visits). Study completion will be analysed post hoc, as a secondary outcome.
i)Demographic data: includes age, gender, method of suicide attempt, employment status, education history, place of residence, living situation, marriage status, family contact, known diagnoses and co-occurring conditions (e.g. drug and alcohol use), and history of service provision, including use of psychological interventions

It is anticipated that a number of people within the study population will be from specific cultural groups, who may also be high-risk populations, such as Aboriginal and Torres Strait Islander people, people from cultural and linguistically diverse (CALD) communities, people who identify as LGBTQI, older persons (aged over 60 years), and young people (aged 16–18 years). Questions are included to enable the identification of these specific target population subgroups.

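### The visit-by-visit comparison of secondary scores does not commit to using the baseline score or earlier visits, so unless the imputation condition is met it rests on those still in follow-up

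*Protocol article*

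**What the plan says.** Under Secondary outcome measures, the article describes the analysis of the self-report scores in one sentence: "Scores will be compared for each group at each follow-up time point". No model, test or covariate is named.

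The data for a fuller analysis are collected. The section on plans for assessment and collection of outcomes {18a} says: "At baseline, demographic data and psychometric data are collected in person or via the telephone with the RA, as outlined below". It then says: "At end of treatment and 6, 12, and 24 months, psychometric data are collected". Alliance is the exception: "Therapeutic alliance is assessed at the completion of the interventions".

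The statistical methods section {20a} is headed as covering both primary and secondary outcomes, but its content is the time-to-event analysis of re-presentation. Its covariate screening rule belongs to that model. Section {20c} adds that missing secondary data will be multiply imputed on two conditions: that missingness is found to be completely at random, and that it is above 10%. The imputation model is not described.

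The Sample size section expects a "dropout rate of approximately 4.5% per month which would result in 35% of participants completing the full 24-month follow-up (65% total dropout").

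**The concern.** Followed as written, the score analysis is a set of comparisons, one per visit, with nothing tying them to the baseline value or to each other. Two things could be lost.

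- **Precision.** If a scale at follow-up correlates with its baseline value, leaving baseline out gives wider intervals than necessary and lets chance baseline differences between arms pass into the estimate.
- **Use of partial follow-up.** Someone who gives a 6-month score and then leaves has information about the later visits. A comparison confined to one visit does not use it. If leaving is related to earlier scores, the people still present are a selected group.

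The imputation rule does not close the second gap. It applies when missingness is completely at random, which is when an analysis of those present is least open to bias. When missingness is not completely at random, no method is stated.

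**Working it through.** **Inputs from the article.** 137 per arm; dropout about 4.5% per month; about 35% completing 24 months; effective dropout 41%; 80% power and two-sided 5% (stated for the primary outcome, used here for illustration).

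**Assumptions, not in the documents.** Baseline-to-follow-up correlation r of 0.3 to 0.7; differences expressed in SD units; a constant monthly dropout rate; nobody who has dropped out gives later scores.

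**1. The plan's own dropout figures.** Retention at 24 months is 0.955^24 = 33.1%, or exp(−0.045 × 24) = 34.0%, in line with the stated approximate 35%. The mean of 0.955^k over months k = 1 to 24 is 0.591, so effective dropout is 1 − 0.591 = 41%, as stated. The 41% describes person-time for the event analysis. For a score at a fixed visit, what counts is the number present at that visit.

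**2. Numbers with a score, per arm.**

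- 6 months: 137 × 0.955^6 = 137 × 0.759 = 104
- 12 months: 137 × 0.955^12 = 137 × 0.575 = 79
- 24 months: 137 × 0.331 = 45, or 137 × 0.35 = 48

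So about 56 to 59 per arm (104 − 48 to 104 − 45) would have a 6-month score but no 24-month score.

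**3. Gain from baseline adjustment.** Adjustment multiplies the variance of the arm difference by 1 − r². The detectable difference is (1.96 + 0.84) × √(2/n) × √(1 − r²). At 24 months with n = 48:

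| r | Variance reduction | Equivalent n per arm | Detectable difference (SD) | Power for 0.5 SD |
|---|---|---|---|---|
| 0 | 0% | 48 | 0.57 | 69% |
| 0.3 | 9% | 53 | 0.55 | 73% |
| 0.5 | 25% | 64 | 0.50 | 81% |
| 0.7 | 49% | 94 | 0.41 | 93% |

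With n = 46 the figures are 0.58 SD unadjusted and 0.51 SD at r = 0.5.

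At r = 0.5 the detectable difference goes from 0.39 to 0.34 SD at 6 months (n = 104) and from 0.45 to 0.39 SD at 12 months (n = 79). The proportional gain is the same at every visit because it depends on r alone.

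**4. Gain from modelling all visits.** This is separate, and the documents do not allow it to be sized: they give no correlations between visits and no pattern of dropout by score. Its direction is clear. Earlier scores inform the later comparisons, and the analysis is valid if missingness depends only on what has been observed.

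**The case against.** The strongest objection is that the article is silent rather than wrong. The sentence says what is compared and when. A baseline-adjusted repeated-measures model that reports each arm against SPP at each visit would also satisfy it, and covariates for secondary outcomes are often left to an analysis plan, which is not shown. This stands in part. A reader might infer that the plan excludes the baseline score, and the text does not support that. What remains is that the one analysis stated has a visit-by-visit form, the methods section headed for secondary outcomes adds nothing on scores, and the missing-data rule leaves a gap.

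Other stronger readings also fail:

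- **That people who drop out contribute nothing later.** Where both imputation conditions are met, they can contribute. Section {20c} also states an intention-to-treat main analysis regardless of dropout, though that alone supplies no value for a missing score.
- **That heavy dropout enlarges the proportional loss from ignoring baseline.** That loss is r² at any sample size, and baseline adjustment does not recover a missing follow-up score.
- **That two thirds are missing throughout.** That figure applies only at 24 months.
- **That a linear model would suit every scale.** The C-SSRS includes behaviour and lethality subscales, for which it is not an obvious choice.

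It is also fair to say that r is unknown. At r = 0.3 the precision gain is small.

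**Conclusion.** The point holds as an improvement to how the secondary analysis is fixed. The stated comparison does not commit to the baseline and earlier scores that the trial collects. Unless missingness is judged completely at random and exceeds 10%, it relies on about 104, 79 and 45 to 48 per arm at 6, 12 and 24 months.

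Baseline adjustment would remove 9% to 49% of the variance for an assumed r of 0.3 to 0.7, independently of dropout. The benefit of modelling all visits is a second, distinct gain: partial follow-up is used and validity needs only missing at random. It does not protect against dropout that depends on unobserved scores.

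The primary time-to-event analysis is unaffected. The retention counts assume a constant dropout rate, and the precision figures rest on the assumed r. An analysis plan not shown may already settle the matter.

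**What to change.** Replace the sentence on comparing scores with wording to this effect:

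- Each continuous scale (DASS-21 subscales, CISS, BRS, IIPSS, C-SSRS intensity of ideation) is analysed by a mixed model for repeated measures over all follow-up visits, with arm, visit, arm-by-visit and the baseline score (and baseline-by-visit if wanted). Each therapy arm is compared with SPP at each visit, with a 95% confidence interval.
- C-SSRS behaviour and lethality items are analysed with a suitable categorical or count model.
- HAqII, which has no baseline, is compared between the two therapy arms only.

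Reconcile section {20c} with this, so that the handling of missing scores no longer depends on missingness being completely at random.

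The cost is analysis wording only. No extra data, visits or participants are needed. The change should be recorded before any scores are compared by arm, so that the choice between adjusted and unadjusted, or visit-wise and longitudinal, results is not made after seeing them.

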### Participant timeline {13}

Please refer to Fig 1 for the ASSIP-CBT study schedule of recruitment, interventions, and baseline and follow-up assessments (SPIRIT figure).

**Fig. 1 Fig1:**
[figure not shown]
SPIRIT figure—ASSIP-CBT study schedule of recruitment, interventions, and baseline and follow-up assessments. *For all participants, including SPP. **Includes ASSIP follow-up letters sent over 24 months after therapy. ***This includes employment status; cultural and linguistically diverse (CALD) status; Aboriginal and Torres Strait Islander and lesbian, gay, bisexual, transgender, intersex, and queer (LGBTQI) status; education history; living situation; known diagnoses; and history of service provision

### Sample size {14}

The sample size was calculated on the basis of a time to event analysis of the time to representation for suicidality. From previous studies using CBT as an additional treatment component following attempted suicide [24, 39], we anticipated that the proportion of patients re-presenting for attempted suicide over a 2-year follow-up period will be approximately half that of the TAU group. From recent data from our health service, this represents a decrease from 48 to 24%. To detect this difference (equivalent to a hazard ratio of 0.42) by the log rank test in a proportional hazards time-to-event analysis with 80% power at a two-sided significance level of 5%, we require 132 participants in two groups of 66 each. However, we anticipated a dropout rate of approximately 4.5% per month which would result in 35% of participants completing the full 24-month follow-up (65% total dropout). The effective dropout rate is thus 41%, as those dropping out later contribute proportionately more. When accounting for this dropout rate, to maintain the same power, a total of 137 participants in each of the three cohorts are required for a total of 411 in total.

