#### Criteria for discontinuing or modifying allocated interventions {11b}

Consumers are made aware (both verbally and written) that they can withdraw consent to participate in the study at any time without any questions asked, or any impact on their ongoing treatment and care. Participants who withdraw from the study are provided with the option of (a) all their collected data being withdrawn from the study or (b) their collected data being used.

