### Methods in analysis to handle protocol non-adherence and any statistical methods to handle missing data {20c}

All participants will be included in the main analysis (intention to treat) regardless of dropout or adherence to the intervention. Only those who withdraw from the study and all their collected data will be excluded from the analysis. Missing data on the secondary outcomes will be handled by multiple imputation if missingness is found to be “completely at random” and > 10%.

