## Trial status

This manuscript refers to study protocol version 1, 5 April 2019. The recruitment for this study started in October 2019. We have recruited 12 people so far. The interventions have also commenced. We are currently at the beginning stages of year 2. Due to the COVID-19 pandemic, we had to pause the trial for 2 months. We also added an amendment to HREC to allow us to recruit via telephone/online methods. Recruitment has now recommenced. Recruitment is expected to be completed at the end of 2022.

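### The 80% power stated for 137 per arm is not the power of this design: 41% of information is discounted for dropout, although the primary outcome is read from ED records for everyone

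*Protocol article*

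**What the plan says.** **Base sample size** (Sample size {14}). The effect is a halving of two-year re-presentation for attempted suicide: "this represents a decrease from 48 to 24" per cent, "equivalent to a hazard ratio of 0.42". For a log-rank test, "with 80% power at a two-sided significance level of 5%, we require 132 participants in two groups of 66 each".

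**Dropout adjustment** (same section). "we anticipated a dropout rate of approximately 4.5% per month which would result in 35% of participants completing the full 24-month follow-up". Because later dropouts contribute more, this is converted to an effective loss of 41%, and the target becomes 137 per arm, 411 in all.

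**How the primary outcome is obtained** (Plans for assessment and collection of outcomes {18a}). "The ED presentations will be interrogated for the UR number of all study participants", covering presentations within 24 months of the initial one. The research assistant's follow-up contacts are for the secondary outcomes.

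**Who is analysed** (section {20c}). "All participants will be included in the main analysis (intention to treat) regardless of dropout or adherence to the intervention". The one exclusion is people who withdraw together with their data; section {11b} offers the option of "all their collected data being withdrawn from the study".

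**What dropout means.** The Sample size section does not say. Under Exclusion criteria, a dropout is someone who completes baseline and then attends no later assessment or treatment session; three or more missed rebookings also count. Secondary outcome measures refers to the Sample size section for the expected low completion rate.

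**End of event-free time** (Primary outcome measures; Statistical methods {20a}). It runs from enrolment to the last assessment, with 24 months in parentheses.

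**The concern.** The dropout adjustment makes sense only if a person who drops out stops supplying time-to-event information. For an outcome found by searching hospital records under a patient number, non-attendance at an assessment or session does not have that effect. The Sample size section therefore deducts information that sections {18a} and {20c} keep.

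Two things are at stake. First, the trial's power statement does not tell a reader what the trial can detect. That matters for a single service which, at the time of writing, reported "We have recruited 12 people so far" against a target of 411. Second, the phrase about the last assessment is unclear for someone who stops attending. The sample-size reasoning points to the last visit attended; the parenthesis, the record search and the intention-to-treat statement point to month 24.

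**Working it through.** **Inputs.** From Sample size {14}: 48% and 24% with an event at 24 months (mean 36%), two-sided 5%, 80% power, dropout 4.5% per month, effective loss 41%, 137 per arm. From Trial design: 1:1:1 allocation, so each intervention against SPP is a 1:1 pair of 274 people.

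1. **Hazard ratio.** ln(0.76)/ln(0.52) = 0.42, as stated.

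2. **Base size.** Freedman's formula is d = (1.960 + 0.842)² × [(1 + HR)/(1 − HR)]². With HR = 0.4197, d = 47 events. Then 47/0.36 = 130.6 people, or 66 per group. This reproduces the protocol's 132. (Schoenfeld's formula gives 42 events and 59 per group, so Freedman's is the one that matches.)

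3. **Effective dropout.** One minus the mean of 0.955^k for k = 1 to 24 is 40.9%, matching 41%. Retention at 24 months is 0.955²⁴ = 33%, or exp(−0.045 × 24) = 34%, close to the stated 35%.

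4. **Inflated size.** 66/(1 − 0.41) = 111.9, so 112 per arm and 336 in total. The stated 137 is not reproduced. Going from 66 to 137 implies a loss of 1 − 66/137 = 52%. The nearest variant found is Freedman's formula at a two-sided 2.5% level: 57 events, 80 per group, 80/0.59 = 136. The protocol states 5%, and 136 is still not 137.

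5. **Power at 137 per arm if 41% were really lost.** Events = 274 × 0.36 × 0.59 = 58.2. Power = Φ(√58.2 × 0.58/1.42 − 1.960) = 88% (Schoenfeld 91%), not 80%.

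6. **Power at 137 per arm with full record follow-up.** Events = 274 × 0.36 = 98.6. Power = Φ(√98.6 × 0.58/1.42 − 1.960) = 98% (Schoenfeld 99%).

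7. **Some loss of the ED-record outcome.** The protocol gives no rate, so 5% to 20% is assumed for illustration:

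| Assumed loss | Per arm for 80% power | Events at 137 per arm | Power at 137 per arm |
|---|---|---|---|
| 0% | 66 | 98.6 | 98% |
| 5% | 70 | 93.7 | 98% |
| 10% | 74 | 88.8 | 97% |
| 20% | 83 | 78.9 | 95% |

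8. **Detectable effect.** With 48% in the control arm and full record follow-up, 137 per arm has 80% power at a hazard ratio of about 0.58, that is 48% against 31%.

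**The case against.** The strongest reply is that nothing harmful follows. The discount makes the trial larger, and a larger trial protects the questionnaire outcomes and guards against an optimistic halving of events. This stands as to direction: the stated power is too low, not too high. It does not rescue the statement, which matches neither the record-based design nor its own 41%.

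A second reply is that the Sample size section never names the type of dropout. That is fair. Reading it as non-attendance is an inference from the Exclusion criteria and Secondary outcome measures sections. But if it means loss of the ED-record outcome, the protocol gives no reason for a loss of that size.

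A third reply is that some outcome information will really be lost. This also stands. Limitations concedes that presentations interstate or in primary care are not captured, participants may withdraw their data, and deaths not involving self-harm count as non-completion. A reader might infer that only withdrawal of record access loses the outcome; the documents do not support that. The zero-loss figures are therefore a best case.

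A reader might also infer that the analysis will censor people when they drop out, so that censoring is informative and intention to treat is breached. No section plans this. The event-free sentence gives 24 months, the record search covers everyone, and section {20c} includes all regardless of dropout. What remains is an ambiguous phrase.

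**Conclusion.** The point holds as a mismatch between the stated power and the design. On the protocol's own event rates and Freedman's formula, 137 per arm has about 98% power for a hazard ratio of 0.42 under full record follow-up, and 95% to 98% if 5% to 20% of outcome information is lost. Separately, 41% leads from 66 to 112 per arm, and at that loss 137 per arm has about 88% power. On neither basis is it 80%.

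The size of the error depends on the true loss of the ED-record outcome, which the protocol does not give, and on reading dropout as non-attendance. The arithmetic gap between 112 and 137 depends on neither. It also means that the move from 66 to 137 cannot be put down to the dropout discount alone. The error is conservative, and nothing here shows that the trial should be cut to 66 per arm.

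**What to change.** In Sample size {14}:
- State the loss that applies to the ED-record outcome (presentations elsewhere, data withdrawal, death not involving self-harm) as an assumption with a range.
- Reconcile 66, 41% and 137.
- Restate the power, or the detectable hazard ratio, at 137 per arm on that basis.
- Keep the 65% total dropout for the questionnaire outcomes only.

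In Primary outcome measures and Statistical methods {20a}, replace the reference to the last assessment with 24 months of ED-record follow-up. Count it from the initial presentation, the origin the protocol already uses for event times and for the record search. State that stopping assessments or therapy is not a censoring event.

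The cost is wording only. Data collection does not change, and the sponsor may keep 137 per arm and justify it by the smaller effect it can detect. The downside is that presentations outside the service stay invisible, so a stated allowance is still needed and its rate will rest on judgement.

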**Methods:**

This is a randomised controlled trial with blinding of those assessing the outcomes. People who attempt suicide or experience suicidality after a suicide attempt, present to the Gold Coast Mental Health and Specialist Services, are placed on the Suicide Prevention Pathway (SPP), and meet the eligibility criteria, are offered the opportunity to participate. A total of 411 participants will be recruited for the study, with 137 allocated to each cohort (participants are randomised to SPP, ASSIP + SPP, or CBT + SPP). The primary outcomes of this study are re-presentation to hospitals with suicide attempts. Presentations with suicidal ideation will also be examined (in a descriptive analysis) to ascertain whether a rise in suicidal ideation is commensurate with a fall in suicide attempts (which might indicate an increase in help-seeking behaviours). Death by suicide rates will also be examined to ensure that representations with a suicide attempt are not due to participants dying, but due to a potential improvement in mental health. For participants without a subsequent suicide attempt, the total number of days from enrolment to the last assessment (24 months) will be calculated. Self-reported levels of suicidality, depression, anxiety, stress, resilience, problem-solving skills, and self- and therapist-reported level of therapeutic engagement are also being examined. Psychometric data are collected at baseline, end of interventions, and 6,12, and 24 months.

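### The step from 66 to 137 per group does not follow from the stated 41% effective dropout; it gives 112, and 137 per arm delivers about 88% power, not 80%

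*Protocol article*

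**What the plan says.** Everything needed is in the protocol article, section Sample size {14}.

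- **Test and error rates:** the calculation is made "by the log rank test in a proportional hazards time-to-event analysis", "with 80% power at a two-sided significance level of 5" per cent.
- **Effect:** re-presentation over two years is assumed to halve; "this represents a decrease from 48 to 24" per cent, described as "equivalent to a hazard ratio of 0.42".
- **Before dropout:** "we require 132 participants in two groups of 66 each".
- **Dropout:** about 4.5% per month, leaving 35% at 24 months. Later dropouts contribute more follow-up, so "The effective dropout rate is thus 41" per cent.
- **After dropout:** "to maintain the same power, a total of 137 participants in each of the three cohorts are required", which is 411 in all.

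The Methods part of the abstract repeats the target: "A total of 411 participants will be recruited for the study, with 137 allocated to each cohort". Dropout is the only reason given for the increase from 66 to 137. The section names no higher power, no smaller significance level and no further allowance.

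**The concern.** The paragraph prints its inputs, the operation and the result, and the result is not what the operation yields. This is therefore not a detail left to a fuller document. The number concerned is the recruitment target for all three arms.

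Two things are at stake. First, a reader cannot tell what power the trial was designed to have: the stated 80% and the stated 137 cannot both be right on the stated inputs. Second, an input may have been used but not reported. If so, it should be known before the primary analysis, because some candidates (a different significance level, for example) would bear on how the two comparisons with SPP are read.

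**Working it through.** **Inputs (Sample size {14}):** 24-month event proportions 0.48 and 0.24; log rank test; two-sided 5%; 80% power; 4.5% dropout per month; effective dropout 41%. Equal allocation is from Trial design.

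**1. Hazard ratio.** ln(1 − 0.24) / ln(1 − 0.48) = ln 0.76 / ln 0.52 = 0.4197. The stated 0.42 reproduces.

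**2. Size before dropout (Freedman).** Events = (1.960 + 0.842)² × [(1 + HR)/(1 − HR)]² = 7.85 × (1.4197/0.5803)² = 7.85 × 5.985 = 47. The mean event proportion is (0.48 + 0.24)/2 = 0.36. Then 47/0.36 = 130.6 in two groups, or 65.3 per group, rounded up to 66. The stated 132 in two groups of 66 reproduces. (Schoenfeld's formula gives 42 events and 59 per group, so it is not the method behind the 66.)

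**3. Effective dropout.** Mean retention over months 1 to 24 at 4.5% per month is the average of 0.955^k for k = 1 to 24, which is 0.591. The effective loss is 0.409, so the stated 41% reproduces. Retention at 24 months is 0.955^24 = 0.33, close to the stated 35% given that the monthly rate is approximate.

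**4. Inflation for dropout.** 66 / (1 − 0.41) = 66/0.59 = 111.9, so **112 per arm and 3 × 112 = 336 in total**. The plan states 137 and 411. The gap is 25 per arm, 75 in total. The dropout that would turn 66 into 137 is 1 − 66/137 = 0.518.

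**5. Other methods at the stated 5% and 80%.** None gives 137:

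| Method | Per arm |
|---|---|
| 66 × 1.41 (a common mistake) | 94 |
| Schoenfeld, 59/0.59 | 100 |
| Log rank with exponential dropout modelled directly (Freedman) | 103 to 106 |
| Two proportions, 62/0.59 | 106 |
| Two proportions with continuity correction, 70/0.59 | 119 |
| Full 65% dropout, 66/0.35 | 189 |

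**6. Power at 137 per arm on the stated inputs.** Effective number per arm: 137 × 0.59 = 80.8. Expected events per comparison: 2 × 80.8 × 0.36 = 58.2. Power = Φ(√58.2 × 0.5803/1.4197 − 1.960) = Φ(3.118 − 1.960) = Φ(1.158) = **0.877**. Schoenfeld gives 0.912, and modelling exponential dropout directly gives about 0.90 (Freedman).

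**7. Changed inputs that come near 137.**

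- Alpha 2.5% per comparison, 80% power (Freedman): 57 events, 57/0.36/2 = 79.2, so 80 per group; 80/0.59 = 135.6, so 136 per arm. Power at 137 is then Φ(3.118 − 2.241) = 0.810.
- 90% power at 5%: Freedman 88/0.59 = 149.2, so 150; Schoenfeld 78/0.59 = 132.2, so 133, but Schoenfeld does not yield the stated 66.
- Rough scaling of 66 by the noncentrality ratio of a two-degree-of-freedom to a one-degree-of-freedom test at 5%: 66 × 9.63/7.85/0.59, about 137.

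**The case against.** The strongest reply is that the error does no harm in the direction that usually matters. On the plan's own assumptions the target is generous: power is about 88% at 5%, and still about 81% if each comparison were tested at 2.5%. Trial status reports only 12 participants recruited at the start of the second year, so a margin may be welcome. This stands. It bears on how serious the point is and argues against cutting the target by reflex, but it does not make the paragraph correct.

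A reader might infer that the trial is underpowered, because the stated power is not what 411 participants give. The documents do not support that; the discrepancy runs the other way.

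A reader might also infer that the trial was really sized at 2.5% for each of two comparisons and that the printed 5% is a mistake, so that the final report must use the stricter threshold. The documents do not support that either. The sample size section states 5%, and no section mentions 2.5%, Bonferroni or any adjustment for the two comparisons. The 2.5% route gives 136, not 137, and the rough two-degree-of-freedom scaling lands as close, so the number 137 does not identify its source. A plain slip, or an unstated allowance for participants who withdraw all their data (allowed under {11b} and excluded from analysis under {20c}), cannot be ruled out.

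**Conclusion.** The point holds as an arithmetic inconsistency in the sample size section. On the stated inputs the final step gives 112 per arm and 336 in total. The printed 137 and 411 exceed this by 25 per arm and 75 in total, and correspond to about 88% power per comparison with SPP rather than 80%. The 112 is simple division of the plan's own figures. The 88% assumes proportional hazards, 48% against 24% at 24 months, and 41% effective dropout applied as a reduction in effective numbers; the alternative methods above put it at about 90% to 91%. On these assumptions neither comparison is short of power. Which input, if any, was left out cannot be settled from the document.

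**What to change.** Check the original calculation and correct the paragraph in one of these ways.

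- **If the stated inputs stand:** keep 137 per arm (411) and state that this gives about 88% power per comparison at two-sided 5% after 41% effective dropout; or state that 80% power needs 112 per arm (336). The first leaves the target unchanged. The second lowers it by 75, about 18% (75/411), and gives up the margin in power.
- **If another input was used:** state it, show the step that gives 137, and carry it into the statistical methods section. For example, if each comparison was sized at 2.5%, the text should say so, with about 136 per arm required and about 81% power at 137. This should be adopted only if the original calculation confirms it, since the document states 5%.

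The Methods part of the abstract needs changing only if the target changes. The cost is a check of the original calculation and a few reworded sentences; no extra participants are needed.
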